• The *caregiver summary assessment of the participant's degree of adherence *will be rated by using the same 5 point ordinal scale used for participants. To improve the validity of adherence ratings, we will complete a systematic assessment of medication use for the last 2 months (to minimize recall bias over the 6 month period); this 2 month adherence will be extrapolated for the last 6 months.

For the economic aspects of the study, we will ask caregivers to complete the Cost of Illness Schedule (CIS) that has been developed and used in India in community studies before[27] at baseline, 6 and 12 months. In addition, we will record the type, dosage and duration of medications prescribed by treating Psychiatrists during each of the contacts with participants as well as the number of inpatient days for each participant - this data will be available from the Psychiatrists' structured records. Service costs will be calculated by attaching locally calculated unit costs to these data. In addition, we will use the Euroqol EQ-5D with participants for assessing Quality of Life Years at baseline and at 12 months.

The adherence measures and the CIS will be repeated at 6 months, as will the IDEAS. For the CIS and adherence measures, the rationale is to minimize recall bias. The IDEAS will be used at 6 months to have an interim measure for one of the primary outcomes that is brief and easy to complete.

Table 2 describes the data collection details of the study.

**Table 2 T2:** Summary table of data collection in COPSI.

TYPE OF DATA					
**1. Quantitative**: (using a combination of programmed palmtops and paper and pencil methods)			**Measured at**:		

**Primary Outcome**	**Interviewee**	**Outcome assessment scale description**	**0 month**	**6 months**	**12 months**

Symptoms	Person with schizophrenia	*Positive and Negative Syndrome Scale (PANSS)*. The PANSS has 30 items to record current psychopathology on 3 domains- positive symptoms, negative symptoms and general psychopathology; each item rated on 1-7 scale thus having a total score range of 30-210.	**X**		**X**

Disability	Primary caregivers	*Indian Disability Evaluation and Assessment Scale (IDEAS)*. For the IDEAS evaluation, the participant is assessed on 4 domains- Self Care, Interpersonal Activities, Communication and Understanding and Work. The scale generates a global score of 0-20 with increasing scores indicating more severe disabilities	**X**	**X**	**X**

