##### Statistical issues

###### Sample size estimation

Based on the data from the earlier non randomized study[9], it was assumed that a difference of at least 20% reduction on the PANSS total score of 65 (sd 10) i.e. 13 points to 52, would be highly clinically significant. The estimated pre-post correlation was 0.4 (reducing the effective sd to 9 after adjusting for baseline). The intra-class correlation within the three sites in the control arm was set at 0.05; in the intervention arm (which would include within-CHW as well as within-site effects) it was set at a higher level of 0.1; alpha was set as 0.05. Using the method of Roberts and Roberts[28] with the Stata routine *cluspower *will give us 98% power to detect this difference. This is equivalent to a large standardised effect size, 1.44. For effect sizes of 1 (9 PANSS units) and 0.8 (7.2 PANSS units) the power would be approximately 90% and 80% respectively.

The required sample size of 241 was increased to 282 to allow for 15% attrition and rounded up to allow for a 2:1 randomisation within each site. The total number of participants was then divided slightly unequally between sites for reasons of feasibility. A total of 188 persons with schizophrenia will be allocated to the CCBC arm while 94 persons will be allocated to the FBC arm.

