##### Data management and analysis

Findings will be reported according to the revised CONSORT guidelines[14]. No interim analyses are planned apart from baseline comparisons. The statistical package Stata will be used for the quantitative analysis. In accordance with good trial practices, data will be retained for 7 years after completion of the trial.

Descriptive summaries of socio-demographic and clinical data will be provided for all trial participants at baseline, and for outcome measures at baseline, 6-month and 12-month follow up points; this will include means and standard deviations, or proportions, in the two arms, as appropriate. Scale and subscale totals with missing items will be pro-rated (i.e. based on the mean of those items that are present) if 20% or fewer items are missing. The PANSS and the IDEAS will be summarised in terms of the total score, the separate sub scores of the different domains and the proportion of patients improving by >20% from baseline. Histograms within each arm will be used to assess normality of the distribution of the data, to identify any outliers and check for data errors. The proportion of participants who are fully, partially or non- adherent to antipsychotic treatment (derived from the adherence ratings of primary caregivers) will be reported for both arms. CHW characteristics such as completed years of education and caseload will also be described.

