The data will be analysed under intention-to-treat assumptions (i.e. all those with at least one follow up measurement will be analysed in arms as randomised). The 12-month PANSS total score, adjusted for PANSS scores at baseline and site (using analysis of covariance), and including clustering effects of CHWs, will be used for determining the comparative effects of the two arms on this primary outcome of the study. The disability score generated by the IDEAS will be similarly analysed; in addition, a longitudinal analysis including both 6- and 12-month outcomes will also be performed using a GEE or random effects model including a time x treatment term allowing for modelling changes over time. Residual analysis will be performed to check the distribution of the data and to detect outliers. Logistic regression analysis with >20% reduction in PANSS at 12 months as the dependent variable will be performed. Secondary outcomes at 12 months will be treated in a similar way to the primary outcome; of the secondary outcomes, adherence will be measured at the 6-month point as well as the 12-month point.

A number of sensitivity analyses for the primary outcome are planned to be carried out. Regression models will be re-estimated including possible confounders such as participant characteristics that differ at baseline and may be associated with outcome (e.g. age, gender, duration of illness, socioeconomic status and education) and CHW characteristics like education and caseload; imputation of missing baseline covariates will be performed if there are more than 10% missing and analyses will be repeated.

Subgroup analyses will include site and gender as interactions with treatment arm to estimate differential effects, and further analyses will investigate the effect of engagement with the interventions on outcome. In addition to the primary intention-to-treat analysis, the effect of participants in the CCBC arm receiving the minimum effective number of sessions as defined in the protocol will also be estimated. Power for these subgroup analyses has not been specifically allowed for, and so they will be treated as exploratory.

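### The >20% PANSS responder is a percentage of a raw total whose minimum is 30, so it is not a 20% improvement and its meaning shifts with baseline severity

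*Protocol article*

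**What the plan says.** In the protocol article, Table 2 (under Quantitative assessments) describes the PANSS as 30 items, "each item rated on 1-7 scale thus having a total score range of 30-210". Under Data management and analysis, both the PANSS and the IDEAS are to be summarised by, among other things, "the proportion of patients improving by >20% from baseline". The same section adds a model for the PANSS only: "Logistic regression analysis with >20% reduction in PANSS at 12 months as the dependent variable will be performed". The formula for percentage reduction is not written out. The one place where a PANSS percentage is worked through is Sample size estimation, where the target is a "20% reduction on the PANSS total score of 65 (sd 10) i.e. 13 points to 52"; that divides by the raw total.

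For the disability scale, Table 2 says: "The scale generates a global score of 0-20 with increasing scores indicating more severe disabilities".

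The primary PANSS analysis is separate from all this: an analysis of covariance of the 12-month total, adjusted for baseline and site, with clustering by community health worker.

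**The concern.** A person with no symptoms scores 30 on the PANSS, not 0. A percentage of the raw total therefore includes 30 points that no treatment can remove. The same 20% raw fall is a larger share of the removable symptoms when baseline is low than when it is high.

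Two things are at stake. First, a reader will take the reported proportion as the share of patients who improved by a fifth, when the rule asks for considerably more. Second, the bar varies with baseline severity, so two patients with the same relative symptom relief can be classified differently.

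The IDEAS starts at 0 and raises a different problem. Percentage change is undefined at a baseline of 0, and a 1-point fall exceeds 20% at any baseline below 5.

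**Working it through.** **Inputs.** From the article: PANSS range 30 to 210 (Table 2); planning mean 65, SD 10, pre-post correlation 0.4, adjusted SD stated as 9 (Sample size estimation). Assumed: normal scores held within the scale limits, the arm means shown below, and a baseline range of 45 to 85 (65 ± 2 × 10).

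**The article's own figure.** 0.20 × 65 = 13; 65 − 13 = 52; 13/9 = 1.44. All three match the article and use the raw total. With the minimum removed, 20% would be 0.20 × (65 − 30) = 7 points, to 58.

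**Share of the removable score needed for a 20% raw fall**, 0.20B/(B − 30) at baseline B:

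| Baseline | Raw 20% fall | Points above 30 | Share |
|---|---|---|---|
| 45 | 9 | 15 | 60% |
| 55 | 11 | 25 | 44% |
| 65 | 13 | 35 | 37% |
| 75 | 15 | 45 | 33% |
| 85 | 17 | 55 | 31% |

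The other way round, take a fall of 35% of the removable score. It is 0.35 × 45 = 15.75 points at baseline 75 (21% raw, a responder), 12.25 points at 65 (19%, not a responder) and 8.75 points at 55 (16%, not a responder). Below 30/0.8 = 37.5 nobody can respond, but that is 2.75 SD below the planning mean: 0.3%, or about 0.8 of 282 participants.

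**Effect on responder rates (simulation, FBC vs CCBC).** Three rules are compared: raw 20%; corrected 20%; and corrected 13/35 = 37%, which is as strict as the raw rule at baseline 65.

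| 12-month means, FBC / CCBC | Raw 20% | Corrected 20% | Corrected 37% |
|---|---|---|---|
| 65 / 57.8 | 10% vs 28% | 24% vs 51% | 8% vs 27% |
| 65 / 52 | 10% vs 50% | 24% vs 73% | 8% vs 50% |
| 60 / 52.8 | 21% vs 47% | 42% vs 70% | 20% vs 47% |

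Across these scenarios, moving from raw 20% to corrected 20% changes the class of about 15% to 23% of participants. Moving from raw 20% to corrected 37% changes only about 2% to 5%.

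**Effect on the arm comparison.** Odds ratios for raw 20%, corrected 20% and corrected 37%:

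- 65 / 57.8: 3.65, 3.24, 4.02
- 65 / 52: 9.3, 8.3, 10.9
- 60 / 52.8: 3.27, 3.19, 3.52

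In the last scenario power, ignoring clustering, with 80 and 160 analysed is 0.98, 0.99 and 0.99. The shifts are modest and not all in one direction.

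**What the correction does not remove.** With FBC unchanged on average, the raw responder rate in the simulation is about 1% near baseline 45, 8% near 65 and 29% near 85; the corrected 20% rule gives 5%, 22% and 54%. Regression to the mean keeps response tied to baseline under either formula, which is a reason to adjust the logistic model for baseline.

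**IDEAS.** 1/B > 0.20 whenever B < 5, and division fails at B = 0.

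**The case against.** Several points on the other side stand.

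- **The threshold drives most of the change in rates.** A reader might infer that the raw rule understates response, because 10% vs 28% becomes 24% vs 51%. That comparison keeps the label 20% while the bar at baseline 65 drops from 13 points to 7. At equal strictness the rates are 8% vs 27%, slightly lower rather than higher.
- **The logistic analysis is not shown to be distorted.** A reader might infer this too. Both arms are judged by the same rule under randomisation stratified by site, so the test of a difference remains valid, and the odds ratios above are similar.
- **The raw rule agrees with the article's own benchmark.** At baseline 65, a 20% raw fall is the 13 points called highly clinically significant. A corrected 20% would count about half of that as response.
- **The extremes are uncommon.** Under the planning values only 2.3% of participants lie below 45 and 6.7% below 50, where more than half of the removable score is needed.
- **Site comparisons.** It is tempting to say that responder rates cannot be compared between sites. The article gives no PANSS severity by site, and all sites share one entry threshold, so this is not supported.
- **The formula may be settled elsewhere.** This is a condensed article, and an analysis plan not shown may define percentage change and the model covariates.

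The last point does not dispose of the matter: the article fixes a >20% reduction as the dependent variable, and its only worked PANSS percentage is on the raw total. For the IDEAS, the rule is only a descriptive summary, no model uses it, and no baseline distribution is given, so the frequency of the problem is unknown.

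**Conclusion.** The point holds in a limited form. On the article's own arithmetic, the PANSS responder is a percentage of a raw total with a minimum of 30, so it is not percentage improvement. It demands 37% of the removable score at the planning baseline and 44% to 33% within one SD of it. The 60% to 31% span rests on the assumed range of 45 to 85.

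The harm is to the meaning of the responder proportion and its dependence on baseline severity. The documents do not support a claim of a biased arm comparison, a distorted odds ratio or a loss of power. The primary analysis of covariance is untouched. The simulated rates depend on the planning mean, SD and correlation and on assumed arm means.

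**What to change.** Define PANSS percentage improvement as (baseline − month 12)/(baseline − 30). Use it for both the responder summary and the logistic model. Adjust that model for baseline PANSS, site and clustering by community health worker, as the primary analysis does. Report the raw-score responder beside it for comparison.

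Fix the cut-off before the data are seen. Keeping 20% on the corrected scale lowers the bar at baseline 65 from 13 points to 7; about 37% (13/35) keeps it level with the 13-point benchmark in Sample size estimation. The text should say which is used and why.

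For the IDEAS, state that the descriptive >20% summary is undefined at baseline 0 and is met by a 1-point fall at any baseline below 5.

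The cost is one formula and a sentence or two of text. No new data and no change in sample size are needed. The downside is that the corrected proportion will not match reports that use the raw rule, which the side-by-side presentation covers.

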### Description of the Interventions

#### The collaborative community based care (CCBC) intervention

The CCBC intervention is underpinned by three key principles:

• firstly, the intervention is planned and implemented for each participant in close collaboration between the person with schizophrenia, the primary care giver(s) and the treatment team members (comprising the lay CHW, a supervising Psychiatric Social Worker and the treating Psychiatrist);

• secondly that the intervention is provided in a flexible manner that reflects the unique needs of the person with schizophrenia and their caregivers and;

• thirdly, that the intervention will promote respect, autonomy and dignity for the person with schizophrenia and caregivers.

The inclusion of the specific treatment components within the treatment package have been guided by:

• evidence that the treatment is locally feasible, acceptable and potentially of low cost;

• evidence for the effectiveness of the treatment in low and middle income settings and;

• evidence that it can be delivered by lay health workers

The CCBC intervention will be coordinated and delivered by lay CHWs who have completed at least 10 years of schooling and have been systematically trained at each site over 6 weeks. The training is based on the intervention manual that follows a modular structure covering various aspects of the illness, specific components of the intervention and the operational requirements of the trial related documentation and supervision http://www.sangath.com/details.php?nav_id=60. The CHWs will be closely supervised at each site by Psychiatric Social Workers working as designated Intervention Coordinators. They will coordinate the overall delivery of the intervention and assure the quality and fidelity of the intervention at the site. The treating Psychiatrists will provide clinical leadership for the community care teams and ongoing supervision to maintain safety and quality standards. Overall, the continued supervision of the CHWs through joint onsite visits, weekly group meetings and in scheduled meetings with the Psychiatrist is an essential component of the CCBC intervention.

The treatments included in the intervention package are:

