#### Facility based Care (FBC)

'Facility Based Care' is the care usually provided by mental health practitioners for persons with schizophrenia and their families. In two of the sites i.e. Goa and Satara, Psychiatrists in the private sector are the primary care providers with trained assistants recording essential socio demographic details in some of these clinics. In rural Tamil Nadu, a team of three persons are involved in the clinics. A trained assistant records essential socio demographic details of all persons who come to the clinic. A brief clinical history is then elicited by the Psychiatric Social worker (PSW) who then presents the findings to the clinic Psychiatrist for detailed assessment and treatment planning. In Goa and in Satara, the Psychiatrists are the first point of contact and, for the most part, conduct all necessary procedures themselves. Across all settings, consultations last from 15-45 minutes; persons with schizophrenia presenting for the first time are reviewed once or twice a month while those who are clinically stable are reviewed more flexibly- once a month- 3 months. Almost all persons with schizophrenia in these facilities are prescribed psychotropic medications with the newer antipsychotic medications being preferred (as in India, these newer drugs are cost comparable with the older antipsychotic drugs) while the use of antidepressants, anticholinergic, sedatives and modified Electroconvulsive treatment (ECT) is based on individual clinical needs. All psychiatrists also provide specific information about the illness, encourage adherence and discuss other specific concerns that the person with schizophrenia or their family members have; all of these are provided on an 'as needed' basis. The salient difference between the two arms is that in the CCBC arm, a complex psychosocial intervention, tailored towards individual needs, will be delivered in an accessible (home based) and structured manner by a dedicated CHW. There will be no guidelines or protocols made available to Psychiatrists for the medical treatment of participants as this is more representative of usual care in India. FBC will continue to be available to participants in both study arms and treating Psychiatrists will be unblinded while providing care for participants.

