#### Implementation

For logistic reasons, the site Data Managers will be responsible for assigning the unique trial ID for each randomized participant in the trial; if the participant is assigned to the CCBC arm, the Data Manager will notify the site intervention coordinator and pass on the required contact information. For participants in both arms, the Data Manager will also ensure that treating Psychiatrists are provided with the specially designed clinical booklet to record treatment details for the next 12 months.

For statistical reasons (see 'sample size estimation' below) there will be unequal allocation, with a larger number in the intervention arm. The rationale for the unequal randomization is the additional source of variability in the intervention arm - the effect of individual community health workers which is built into the analysis and allowed for in the sample size as recommended in the recent CONSORT guidelines for non pharmacological trial design and reporting[15]. It is difficult to precisely estimate the magnitude of this extra variability (the intra-class correlation), but the value chosen for the intervention arm of 0.1 is conservative: a recent review of a large number of primary care variables found the inter-quartile range to be 0 to 0.032[16]. For practical reasons, the ratio of numbers in the two arms was fixed at a whole number; for the study this has been chosen to be 2:1. The method of allocation will be through the use of permuted blocks, with random block sizes chosen from 3, 6 and 9 using the '*ralloc*' routine in Stata.

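### CHW education and caseload are classed as confounders in the two-arm sensitivity model for the primary outcome, although they exist only in the CCBC arm and arise after allocation

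*Protocol article*

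**What the plan says.** Data management and analysis sets the primary comparison as an analysis of covariance of 12-month PANSS on baseline PANSS and site, allowing for clustering by CHW. No CHW characteristic enters that model.

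Sensitivity analyses for the primary outcome follow: "Regression models will be re-estimated including possible confounders such as participant characteristics that differ at baseline and may be associated with outcome". After some examples of participant characteristics, the same list continues with "and CHW characteristics like education and caseload; imputation of missing baseline covariates will be performed if there are more than 10% missing". The text does not restrict the CHW terms to one arm and gives no coding for FBC participants.

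Other sections show who has a CHW:
- Facility based Care (FBC): "The salient difference between the two arms is that in the CCBC arm, a complex psychosocial intervention, tailored towards individual needs, will be delivered", and the sentence goes on to name a dedicated CHW as the person who delivers it.
- Implementation (under Randomisation): "if the participant is assigned to the CCBC arm, the Data Manager will notify the site intervention coordinator". This step comes after allocation.
- Implementation also describes "the additional source of variability in the intervention arm - the effect of individual community health workers".
- The CCBC section says that delivery is by "lay CHWs who have completed at least 10 years of schooling".

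**The concern.** A confounder is a common cause of treatment and outcome, or a proxy for one. In a randomised comparison, a variable that comes into being because of allocation, and in one arm only, cannot be that. CHW education and caseload describe how the intervention was delivered. They may explain why some CCBC participants do better than others, but they cannot explain away a difference between the arms.

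The difficulty goes beyond the label. A regression with an arm term and a covariate that is undefined in one arm has no arm coefficient until someone decides what value the control participants receive, and that decision determines what the coefficient means. A sensitivity analysis is supposed to show whether the primary result is robust. Here it would reflect a coding choice.

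A smaller issue sits in the same sentence. Participant covariates are described as "possible confounders such as participant characteristics that differ at baseline and may be associated with outcome", so the adjustment set depends partly on imbalances seen in the data.

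**Working it through.** The protocol states no figure for this model, so there is none to reproduce. The check asks what the arm coefficient means under each way the CHW variables could be entered for FBC participants.

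**Inputs from the protocol.** 188 CCBC and 94 FBC participants, 282 in all; SD 9 PANSS points after baseline adjustment (both from Sample size estimation); CHW schooling at least 10 years (CCBC section).

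**Coding 1: missing in FBC.** The share without a value is 94/282 = 33.3%, which is the whole control arm. A complete-case fit keeps CCBC only. The arm indicator is then constant and collinear with the intercept (two columns, rank 1), so no treatment effect can be estimated.

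**Coding 2: zero in FBC.** The model is y = a + b·arm + c·E, with E = CHW schooling in CCBC and 0 in FBC. The fitted arm difference at the mean schooling of the CCBC arm is b + c·mean(E). Hence b = (unadjusted difference) − c·mean(E), which is the difference at a CHW with 0 years of schooling. That lies outside the required range.

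Size, with inputs that are *assumed*: 9 CHWs of 18 patients, 80 controls, schooling 10 to 15 years (mean 12.5), ICC 0.1, outcome in SD units.
- Variance of a CHW mean: 0.1 + 0.9/18 = 0.15.
- Unadjusted difference: variance 0.15/9 + 1/80 = 0.0292, SD 0.17.
- Slope SE = √[0.15/(8 × Var E)]. Whole years 10 to 15 give Var E = 35/12 = 2.92 and SE 0.080. A continuous uniform gives Var E = 25/12 = 2.08 and SE 0.095.
- SD of b = √[0.0292 + (12.5 × SE)²] = 1.02 and 1.20 respectively.

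A simulation of 4,000 trials under these assumptions, with whole years of schooling, gave 0.173 without the covariate and 1.118 with it.

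A second simulation used other assumptions: 2,000 runs per scenario, 9 CHWs, schooling 10 to 17 years, caseload 15 to 25, both covariates entered, CHW ICC 0.05, SD 9, true effect −9 points at the average CHW, and baseline PANSS and site left out.

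| Assumed CHW slopes | Unadjusted: mean (SD) | Zero coding: mean (SD) | Centred in CCBC: mean (SD) |
|---|---|---|---|
| none | −9.04 (1.41) | −8.52 (10.83) | −9.04 (1.41) |
| −0.5 points per year of schooling | −9.02 (1.42) | −1.95 (10.37) | −9.02 (1.42) |
| −0.5 per year, +0.2 per case | −8.95 (1.46) | −6.12 (10.35) | −8.95 (1.46) |

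In SD units the spread goes from 1.41/9 = 0.16 to between 10.35/9 = 1.15 and 10.83/9 = 1.20. The shift in the mean agrees with the algebra: −9 + 0.5 × 13.5 = −2.25 for the second row, and −2.25 − 0.2 × 20 = −6.25 for the third.

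**Coding 3: centred at the CCBC mean, 0 in FBC.** Now mean(E) = 0 in CCBC, so b is the unadjusted difference. The last column of the table shows this. The coefficient can be read as the effect at the average CHW, but the adjustment has done nothing to it.

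**The case against.** The strongest reply is that the article gives no coding, and that the coding of a covariate in a sensitivity model is a detail commonly left to a full plan that is not shown. With centring, the coefficient is interpretable and equals the unadjusted one. This stands in part. It rules out saying that the adjusted effect can never be interpreted. It does not rescue the text, because the article does more than leave out a coding: it puts these variables among the confounders of a two-arm comparison. A full plan would have to withdraw that, and under the one benign coding the analysis tests nothing.

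Three stronger readings are tempting, and the document does not support them.
- A reader might infer that the 10% rule would give FBC participants an imputed CHW, since 33.3% lack one. The rule is worded for baseline covariates. Caseload arises after allocation, and an attribute of a CHW whom the participant never had is not applicable rather than missing.
- A reader might infer that the model must either fail to run or appear to overturn the primary result. Centring is a third possibility. Under zero coding with no CHW effect, the mean stays at −8.5 against −9.0. It moves materially only if CHW slopes are assumed, and so wide an interval would be plain to see.
- A reader might infer that the primary result is at risk. The primary model contains no CHW covariates.

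It is also fair to say that the inflation figure applies to one coding, and that the number of CHWs and the spread of their schooling are not in the protocol. On the participant covariates, the text also requires a plausible association with outcome and applies only to sensitivity analyses, so that point is secondary.

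**Conclusion.** The point holds as a misclassification with a practical consequence. CHW education and caseload exist in one arm only, arise after allocation and cannot confound the randomised comparison. Until a coding is fixed, the adjusted arm effect has no defined meaning, and none of the three codings yields an informative between-arm adjustment. This conclusion rests on the protocol alone.

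The size is illustrative. Under zero coding and the assumptions listed, the SD of the arm coefficient rises from about 0.17 to about 1.1 SD units (1.0 to 1.2 across the variants shown). A different number of CHWs or spread of schooling would change the figure, but not the fact of extrapolation.

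The scope is limited to the sensitivity analyses of the primary outcome. The primary analysis of covariance and the sample size are untouched. The correction should be made because a named robustness check ought to be able to inform on robustness.

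**What to change.** Revise one sentence in Data management and analysis.

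1. Remove CHW characteristics from the between-arm sensitivity model.
2. Examine CHW education and caseload within the CCBC arm only, mean-centred, with a random effect for CHW, and label this exploratory.
3. Prespecify the participant covariates and enter them whatever the observed balance. The examples already given (age, gender, duration of illness, socioeconomic status, education) could serve. The text offers them only as examples, so the final list needs a decision before unblinding.

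No new data are needed, since the same section already plans to describe CHW education and caseload. The cost is the rewording.
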